## **STUDY PROTOCOL**

### **Title of Research Project: Impact of exercise on ovarian cancer prognosis**

#### **RESEARCH PLAN**

1. **Statement of Purpose:** State the scientific aim(s) of the study, or the hypotheses to be tested.

**Primary Aims:** To examine, in 230 women who have completed treatment for Stage I-IV ovarian cancer, the impact of a moderate-intensity aerobic exercise intervention vs. health education on:

- *Quality of Life*
- *Body Composition* (weight, BMI, total and % body fat, waist and hip circumference)
- *Serum Hormones* possibly associated with physical activity and ovarian cancer prognosis (insulin, IGF-I, IGF-II, IGF binding protein-3, CRP, leptin, osteopontin, MIF, prolactin, and CA-125)
- *Diurnal Salivary Cortisol* which is a marker of stress

#### **Secondary Aims:**

**a)** Among the women deemed not eligible or who are not interested in participating in the exercise study, to examine baseline associations among:

- *Quality of Life*
- *Lifestyle (physical activity, diet, weight and BMI)*
- *Demographic and prognostic characteristics (e.g., age, disease stage)*

**b)** Obtain information on the role of tumor characteristics in the prognosis of ovarian disease in women randomized to the exercise program or the health education program.

**c)** Validate the lymphedema questionnaire using the volumetric assessment obtained using a Perometer. Evaluate the effect of exercise on lower body lymphedema.

2. **Background:** Describe the background information that led to the plan for this project. Provide references to support the expectation of obtaining useful scientific data.

#### **Ovarian Cancer:**

Ovarian cancer is the fourth most frequent cause of cancer death in women, after lung, breast and colorectal cancer (1). It is difficult to treat, as patients frequently present late in the course of the disease, which may be asymptomatic until advanced stages. More than 90% of women with Stage I ovarian cancer will be cured of their disease, but unfortunately only 20% present with localized disease. Advanced disease outside the pelvis portends a poor prognosis and represents the majority of the estimated 15,000 deaths in 2007 (1).

The current standard treatment of ovarian cancer is to optimally debulk the disease surgically and follow with adjuvant chemotherapy. Standard initial therapy most often is five to six courses of systemic chemotherapy with a platinum and taxane regimen. This treatment approach results in a complete clinical response to therapy in 70%-80% of patients with advanced stage disease (31). Despite the often seen dramatic clinical response to treatment, the disease will recur in 60%-85% of patients diagnosed with advanced disease (1). Unfortunately, no proven curative therapy exists for this group of patients, and the optimal treatment approach for those who relapse after initial treatment remains unknown. However, a growing number of new chemotherapeutic agents in recurrent advanced ovarian cancer have been successful at stabilization of disease and thus are allowing recurrent ovarian cancer to be treated as a chronic disease. In turn, the goals of treatment for women with ovarian cancer are to increase survival and disease-free intervals and to improve quality of life.

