#### **Physical Activity and QOL in cancer survivors:**

Several systematic reviews have indicated the importance of physical activity for the physical and psychological health, and overall QOL of cancer survivors (8,9). Randomized trials in breast cancer survivors have suggested that exercise can lead to improvements in QOL, fatigue and cardiovascular fitness. However, few studies have examined physical activity and QOL in ovarian cancer survivors (10). The American Cancer Society has recently recommended that cancer survivors should perform 30 to 60 min of moderate to vigorous physical activity at least 5 days per week (7). The evidence from studies of breast cancer suggests that few cancer survivors reach these targets, but that those that do reach them report higher QOL than inactive survivors (8,9). Recently, Stevinson and colleagues estimated the prevalence of physical activity in ovarian cancer survivors and examined the relationship between physical activity and QOL in 359 ovarian cancer survivors (10). Approximately 31% of ovarian cancer survivors were meeting the public health physical activity guidelines, and being older, having a higher BMI, a diagnosis within the past five years, and a higher stage of disease were associated with lower physical activity levels. Furthermore, women meeting current physical activity guidelines reported significantly better QOL than those not meeting guidelines. Their finding of an approximate 12 point higher QOL associated with higher physical activity levels compared to women with lower physical activity levels is clinically meaningful. A recent chemotherapy trial reported an increase of 10 points in QOL, suggesting that 10 points represents a meaningful improvement in QOL (37). However, due to the observational nature of their study, it is unknown if the strong association between physical activity and QOL indicates that physical activity contributes to QOL; that QOL leads to greater physical activity; or if other variables are responsible for this association. Given the promising results from randomized controlled trials of exercise in breast cancer survivors, their results suggest that a trial examining the potential causal role of physical activity in improving QOL in ovarian cancer survivors is warranted.

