**Baseline Clinic Visit :** After completion of the baseline visit, in CT the participant will be scheduled (ideally within one week) for a baseline visit at the study center (HRU at YNHH) which will include a DEXA scan to measure total body fat and bone mass and a perometer test to assess leg lymphedema. A binder containing all current IRB approval letters from all participating hospitals will be kept at the

HRU. This can be used by all staff to verify that signed consents from all hospitals are current as some consents are not date stamped.

In Boston the visits will be combined. The participants will also be instructed to fast for 12 hours prior to the visit, not to drink alcohol within 48 hours of the visit, and to refrain from strenuous exercise within 24 hours of the visit. Participants will have ~ 30 ml of blood drawn into 4 vacutainer tubes which will be centrifuged and processed for storage at -70° C as soon as possible following blood draw. Research staff will also review the physical activity and pedometer logs to confirm clarity and completion of the forms. Height, weight, right and left leg circumference and leg length will also be measured.

**D.7B Women enrolled in observational study ONLY (CT residents only):** Among the women screened, but deemed not eligible or interested in participating in the exercise trial, we will invite them to complete a one-time mailed questionnaire (takes ~20 min to complete). One week after mailing the questionnaire, we will follow up with a phone call to confirm receipt of the questionnaire and to answer any questions regarding the study. A stamped, addressed envelope will be provided.

**D.8. Randomization:** Women will be randomized into one of 2 study groups using a random permuted block design of varying block size in a 1:1 ratio (N=115 to intervention, 115 to controls). To ensure women with similar characteristics are equivalently assigned to the 2 groups, we will stratify on menopausal status (at diagnosis) and randomize within each stratum. The following study personnel will be masked to participant study group: staff conducting the baseline interview, conducting the DEXA scan and blood draw, reviewing forms and entering data.

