4. **Statistical Considerations:** Describe the statistical analyses that support the study design.

**Statistical Analyses: Exercise vs. health education study.** We will perform Analysis of Covariance (ANCOVA), with each woman's change in outcome (final value – baseline) modeled as a function of treatment group. Each variable listed in the Primary Aims section above will be examined in this fashion. The hypotheses will be tested according to the intention-to-treat philosophy in which all randomized participants will be grouped according to their intervention assignment at randomization, regardless of compliance or adherence to the study. Secondly, mixed effects models for correlated outcomes will also be used to model the data collected on the absolute change in the outcome measures using all time-point differences. Prior to fitting these models, we will perform exploratory data analyses focusing on the distributions of hormone levels by time and intervention group, assessing the appropriateness of log-transformation. Age, prediagnosis menopausal status, race/ethnicity, baseline BMI, and disease stage will be examined as potential covariates to be included in multi-variable adjusted analyses. Among women randomized to exercise, we will also examine effects of exercise on endpoints stratified by adherence (assessed from the DALs) and other measures of compliance (pedometers and PAQ). To explore the potential for effect modification, we will consider stratifying the effect of exercise on endpoints by menopausal status. Two-sided tests will be used for significance. From the food frequency questionnaires, we will identify participants who change their total caloric intake during the study period, and will assess the effect of exercise on outcomes, controlling for change in total caloric intake. Since we are assessing multiple secondary outcomes, we will consider using Bonferroni correction. Although we do not anticipate an appreciable number of participants lost-to-follow-up because of our plan for tracking participants our plan for missing data handling is as follows. The primary mixed model analyses will be performed using all available data, which assumes missing data are missing at random (86). Under this mechanism, the probability of lost-to-follow-up depends on the observed data. Non-random or informative lost-to-follow-up occurs when there is a correlation between the probability of lost-to-follow-up and missing data.

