**Power and Sample Size Considerations:** With a sample size of 230 (which accounts for a potential 30% drop-out/lost to follow up rate) we will have at least 80% power to examine the effect of exercise on QOL and circulating hormones. Our exercise interventions in breast cancer survivors have yielded attrition rates of ~ 10%. Exercise interventions in other cancer survivors (e.g., colon, prostate, and lymphoma) have also yielded similar attrition rates. We hypothesize that attrition may be slightly greater (i.e., 20%) in ovarian cancer patients given their potential for advanced disease, worse QOL and reduced prognosis. However, because no exercise trial has been conducted in ovarian cancer survivors, we now plan to over-recruit to account for a potentially higher attrition rate (30%), and have therefore increased our sample size to N = 230.

In our exercise trial in postmenopausal women, QOL measured by SF-36 was  $79.95 \pm 14.88$  (72). Assuming a 10% effect size, we would need 54 subjects per group or 108 in total. Taking a 30% potential drop-out rate into consideration, then a sample size of 155 is necessary. A 10% between group effect size was observed in Courneya and colleagues recent publication of physical activity and QOL in ovarian cancer survivors (10). A difference of 10 points is clinically meaningful given a recent chemotherapy trial reported an increase of 10 points in QOL, suggesting that 10 points represents a

meaningful improvement in QOL (37). For insulin, Ligibel recently showed a 28% effect size (2.9  $\mu$ U/mL) and standard deviation of 8.0  $\mu$ U/mL, which yields a per group sample size of 80 or total N = 160 (71). Considering the potential for a 30% drop-out with a sample size of 230, a sample size with complete data on 160 women will provide at least 80% power for insulin. For the other hormones, if we assume a 20% effect size, then based on means and standard deviations of these hormones in ovarian cancer survivors (18-20,22,23,47,48,50-55), a sample size of 230 will provide 80% power.

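### Disease stage is collected, but adjustment for it is left open; it should be a pre-specified term, with the stratifier, in the primary models

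*Protocol*

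**What the plan says.** **Eligibility and data.** Stages I to IV are all eligible (Table D.1). Clinical stage is obtained from a physician report or from medical records (D.11).

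**Randomization.** D.8 uses permuted blocks, 115 women per arm, with one stratifier: "we will stratify on menopausal status (at diagnosis) and randomize within each stratum".

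**Analysis.** Section 4 describes an ANCOVA of each woman's change from baseline, and treatment group is the only term it names. A mixed model comes second, although the missing-data text later calls the mixed model primary. Stage appears only in a list with age, menopausal status, race/ethnicity and BMI: "baseline BMI, and disease stage will be examined as potential covariates to be included in multi-variable adjusted analyses". No rule says when a listed factor enters. The missing-data plan assumes missingness at random given the observed data.

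**Why stage might matter.**
- Section 2, Ovarian Cancer: "More than 90% of women with Stage I ovarian cancer will be cured of their disease", whereas in advanced disease "the disease will recur in 60%-85% of patients diagnosed with advanced disease".
- Section 2, late effects and QOL: marked QOL change is said to reflect heavier disease burden.
- Section 2, physical activity and QOL: in a cited survey, "a higher stage of disease were associated with lower physical activity levels" (with other factors).
- Section 4, power: attrition in ovarian cancer patients is expected to be somewhat higher than in other cancer survivors, "given their potential for advanced disease, worse QOL and reduced prognosis".

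**The concern.** The protocol treats extent of disease as relevant to QOL, to activity and to staying in the study, and it collects stage. It does not commit to using stage in the analysis. Three things are at stake.

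1. **Selective adjustment.** With five candidate covariates, no inclusion rule and more than a dozen Primary Aims variables, adjusted or unadjusted results could be emphasised after the estimates are known.
2. **Precision.** If stage predicts six-month change, leaving it out adds residual variance and lets a chance imbalance in stage shift the realised estimate. The same applies to menopausal status, which is balanced by design but is not a fixed model term.
3. **Missing data.** The sample size allows for 30% loss. Missingness at random is assumed given what the model contains. If loss depends on stage, the assumption is easier to defend with stage in the model. The arm contrast is at risk mainly if stage-related loss differs between arms.

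**Working it through.** **Inputs from the protocol (Section 4, D.8).** 115 per arm; 30% loss, so about 160 completers or 80 per arm; SF-36 mean 79.95, SD 14.88, 10% effect; insulin difference 2.9, SD 8.0; two-sided tests.

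**Assumptions, because the protocol gives no figure.** Alpha 0.05. Early-stage share p from 0.20 to 0.50; the 20% localized in Section 2 refers to all patients at presentation, not to trial participants. Gap d between early and advanced stage in six-month change: 0.5 SD, range 0.3 to 0.8.

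**1. The plan's own figure.** n per group = 2(1.96 + 0.842)² × (14.88/7.995)² = 54.4, so 55; the protocol has 54. Then 108/0.7 = 154.3, so 155, as stated. The QOL calculation reproduces. Planned standardized effects are 7.995/14.88 = 0.537 for QOL and 2.9/8.0 = 0.3625 for insulin.

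**2. Chance imbalance in stage.** The SD of the difference in early-stage share is √(2p(1−p)/n). At n = 115 this is 5.3 points (p = 0.20) to 6.6 points (p = 0.50). By exact binomial calculation, the chance of a difference of 10 points or more is 5.8% to 12.9%. At 80 completers per arm it is 13.8% to 23.6%, if loss is unrelated to stage.

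**3. Effect of such an imbalance.** Shift = 0.10 × 0.5 = 0.05 SD. That is 0.05/0.537 = 9% of the planned QOL effect and 0.05/0.3625 = 14% of the insulin effect. The standard error at 80 per arm is √(2/80) = 0.158 SD, so the shift is about a third of one standard error.

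**4. Information gained by adjusting.** With d in within-stage SD units, R²/(1−R²) = p(1−p)d². Multiplied by 160 completers:

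| Early-stage share | d = 0.3 | d = 0.5 | d = 0.8 |
|---|---|---|---|
| 0.20 | 2.3 | 6.4 | 16.4 |
| 0.35 | 3.3 | 9.1 | 23.3 |
| 0.50 | 3.6 | 10.0 | 25.6 |

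The central gain is 6 to 10 completers, range 2 to 26.

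**5. Power.** For QOL, take stage gaps of 4 to 12 SF-36 points (4/14.88 = 0.27 SD to 12/14.88 = 0.81 SD). Adjustment then lowers the required n from 55 to between 54 and 46 per arm. Power at 80 per arm rises from 92.5% to between 92.8% and 96.0%. For insulin with the stated 2.9 and 8.0, power at 80 per arm is 63%; an R² of 2% to 15% raises it to between 64% and 70%. These insulin inputs need 120 per group rather than the stated 80, which is a separate matter.

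**The case against.** **Against the concern.** Randomization makes the group-only test valid, and its standard error already allows for chance imbalance. Modelling change removes stable differences in level between stages, so only a difference in six-month change matters, and the protocol reports none. Participants have finished adjuvant therapy, can exercise and have physician consent, so contrasts in the general patient population need not carry over. The final covariate list is often settled in a statistical analysis plan, which was not available here. Menopausal status is also a reasonable stratifier, since Section 4 considers effect modification by it.

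All of this stands, and it limits the point to a modest one. It does not remove it: Section 4 does address covariates, and what it states is discretionary.

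**Stronger readings that the documents do not support.** A reader might infer that stage is the main driver of the trial's outcomes and of drop-out. The cure and recurrence figures do not show that. Section 2 says survival is not a primary aim, and no section gives six-month change or loss by stage. The attrition sentence compares ovarian cancer patients with other survivors, not stages within the trial. A reader might also infer that omitting stage from the strata leaves the comparison uncontrolled or is a design error. Randomization answers the first part. On the second, Table D.1 admits every stage and D.11 gives no timing for obtaining stage, so the protocol does not show that exact stage is confirmed before randomization. Stratifying on it would also not guarantee balance among completers if loss depends on stage.

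**Conclusion.** The concern holds as a weakness in pre-specification and efficiency; it is neither an error nor a contradiction. The protocol gives qualitative reasons to expect stage to matter and collects it, but fixes neither stage nor its own stratifier as a model term.

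The precision gain is small in the central case and depends wholly on the assumed stage mix and stage gap. The firmer benefits are that the covariate choice no longer depends on the data, and that missingness at random becomes more credible if loss is related to stage. Neither can be given a number from the protocol. Because the remedy is nearly free, the change is worth making.

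**What to change.** In Section 4, state that stage (I-II versus III-IV) and menopausal status at diagnosis enter as fixed terms in both the ANCOVA and the mixed model for every Primary Aims variable. Naming both models matters because the text does not settle which is primary. Present the unadjusted comparison as supportive. State how a woman with unobtained stage is handled. Make the change before outcomes are examined by arm; if a statistical analysis plan already fixes these terms, align the protocol with it.

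The cost is one or two degrees of freedom and no new data item.

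Stratifying randomization on stage is optional, and sensible only if stage is confirmed before randomization. It would give four strata and might need an added verification step. If randomization has begun, the model change alone is enough.

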#### **Late and Long Term Effects of Treatment, Quality of Life (QOL) Issues and Ovarian Cancer:**

Because survival time for ovarian cancer has been so short until recently, little opportunity has existed to study or intervene to improve late and long term effects of treatment or QOL among these patients. However, because of advances in therapeutic modalities, now is the opportune time to begin to identify ways that patients maximize their QOL. Studies are needed to develop and test interventions to improve QOL in ovarian cancer survivors.

[name], a co-investigator on the proposed study, and colleagues discussed in their study, “The Silent Killer: Psychological issues in Ovarian Cancer,” that because of the stage at presentation as well as aggressive surgery and chemotherapy regimens, vulnerability to psychological morbidity, or poor QOL, is higher in women with ovarian cancer (see Section C.4) (32). Furthermore, research has shown poor QOL, measured shortly after completion of chemotherapy, to be a negative prognostic factor in advanced ovarian cancer for overall survival (33). Significant changes in QOL likely reflect greater disease burden and therefore worse outcome.

QOL for patients with ovarian cancer has also been shown to correlate with the number of physical symptoms, primarily fatigue, experienced (34). The trajectory of fatigue in women with ovarian cancer has been studied; women report that fatigue continues even after completion of treatment (35). Interventions to improve physical symptoms, fatigue and overall QOL in ovarian cancer survivors are paramount. Physical activity has been shown to improve fatigue and other physical symptoms, as well as overall QOL, in breast cancer survivors (8,9,36); yet, no study has examined the effect of increasing physical activity levels on fatigue and QOL in ovarian cancer survivors.

In addition to fatigue, other late and long term effects of ovarian cancer surgery and/or treatment include peripheral neuropathy. The recent landmark report of the results of a large randomized trial demonstrating the impressive favorable impact on survival associated with the administration of a platinum agent plus paclitaxel in recurrent, potentially platinum-sensitive ovarian cancer, has appropriately focused attention on concerns for the development of chemotherapy-induced peripheral neuropathy. In this trial, 20% of patients treated with a platinum agent (generally carboplatin) and paclitaxel developed neuropathic symptoms of grade 2 or greater severity, compared to an incidence of only 1% for women administered single agent platinum therapy. Thus, these data suggest that with the current “standard approach” to the management of treatment-associated neuropathy, women receiving this combination regimen shown to improve survival in recurrent ovarian cancer, have a one in five chance of experiencing discomfort, related to neurological toxicity. The National Cancer Institute (NCI) Common Toxicity Scale defines grade 2 sensory neuropathy to be “objective sensory loss or paresthesia (including tingling), interfering with function, but not interfering with activities of daily living.” Once numbness, tingling, and pain develop, the symptoms may persist for months following the discontinuation of treatment, or they may become permanent, even if ultimately reduced somewhat

in severity. Thus, peripheral neuropathy may significantly compromise QOL in ovarian cancer patients. Whether exercise has a favorable impact on QOL, especially among ovarian cancer patients experiencing peripheral neuropathy, is unknown. In the proposed study, we will ask women at baseline and throughout the study if they are experiencing any peripheral neuropathy. If so, then, for women randomized to exercise, we will adapt/modify the exercise program accordingly. For example, we may recommend that the participant exercise with supervision at the health club or cancer survivorship clinics. We may also recommend other activities such as swimming, stationary recumbent bicycling or upper body ergometry.

Lastly, lower body lymphedema has also been reported in some, but not all studies. Most recently, [name] (a co-investigator on the proposed study) and colleagues published results from their 6-month randomized clinical trial of a nursing intervention (tailored specialized care to assist patients in developing self-management skills post-ovarian cancer surgery) vs. health education in 145 women diagnosed with ovarian cancer. In their study, none of the women reported lower leg lymphedema at baseline or 6-months. There is a paucity of research on the incidence and impact of lower body lymphedema in the ovarian cancer population. Lymphedema can be an indicator of recurrence and is frequently associated with toxicities such as skin breakdown, pain, neuropathy, and myopathy. Despite these clinical findings, no systematic study of lower body lymphedema in women with ovarian cancer has been conducted. Whether lower body lymphedema is as debilitating and long-term as post-mastectomy lymphedema is not empirically known. For the proposed study, we will adapt or modify the exercise program for women experiencing lower body lymphedema (e.g., if walking at a certain intensity appears to aggravate it, then we will decrease the intensity and/or recommend other activities such as swimming, recumbant bicycling or upper body ergometry (see Section D).

